### Statistical methods

The non-parametric Mann-Whitney u test will be used to compare the intraoperative BL values between both treatment groups.

The Fisher’s exact test will be performed to compare the rates of 30-day mortality, bile leakage, intraoperative transfusion requirements, and blood transfusion requirements within the first three postoperative days between both treatment groups.

Depending on the distribution of the quantitative parameters intraoperative BL per resection plane size, duration of surgical procedure, and duration of hospital stay the T-test in case of a normal distributed parameter or the non-parametric Mann-Whitney-U-Test will be used to compare both treatment groups.

The postoperative ALT levels, total bilirubin levels, and INR at day 1 and at day 3 will be compared between both treatment groups using the T-test or the Mann-Whitney-U-Test. The Bonferroni-Holm method will be used to adjust the *p*-values.

Two-sided p-values < 0.05 will be considered as statistically significant.

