### Randomization

#### Randomization process

The randomization will facilitate numbered, opaque envelopes, derived from a computer-generated random list by a member of our institution who is not involved in the trial otherwise. After the surgeon has performed the laparotomy and verified that the resection can be performed as planned without any impediments to the trial treatments, the KSC will be informed. The allocation to the treatment or control group in a 1:1 ratio will be done by a member of the KSC by opening the respective envelope and immediate informing of the operating team about the result. The result of the randomization will be recorded in the CRF. The stratification used for randomization is the type of resection: left / right hepatectomy.

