### Sample size

In our institution major liver resections are commonly performed without PM. Based on the intraoperative course, e.g. if extensive BL during parenchymal resection occurs, PM is performed according to the surgeon’s appraisal. In a retrospective analysis of 193 major liver resections that were performed in our institution from January 2011 until February 2014, we found a reduction of the mean intraoperative BL of 27.4% (647 (+/− 612) vs. 891 (+/− 783) ml) in the 62 cases with PM. Since PM was only used when an extensive, uncommon BL was detected, we expect the effect of PM to be substantially higher among standard major liver resections in general. Even though it is a generally accepted fact that blood loss and PRBC transfusions during liver surgery negatively affect patients’ outcome, it is uncertain if the effect is straight proportional. In a recent work Wehry et al. showed that the average amount of blood loss in 186 patients undergoing liver resection was reduced by approximately 400 ml if transfusions were not required [10]. In this context it appears reasonable that this interventional trial should be designed powerful enough to detect a reduction of blood loss of at least 400 ml. The sample size calculation for this trial is therefore based on the assumption that a reduction of the intraoperative BL has to be at least 50% (a reduction of approximately 450 ml) to be clinically relevant. Therefore, 53 patients have to be analyzed in each group to detect a 50% reduction of BL at a standard deviation of 94.1%, an alpha of 5% and an 80% power level. Assuming a realistic dropout rate due to intraoperative findings, contraindications for major liver resection and other reasons 155 patients are planned to be screened and asked for participation in the trial.

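### The primary Mann-Whitney test ignores the left/right strata used in randomisation: a possible loss of power, not a threat to validity

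*Protocol article*

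**What the plan says.** Three places in the protocol article bear on this.

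- **Randomization process.** Allocation is 1:1 from "numbered, opaque envelopes, derived from a computer-generated random list". There is one stratification factor: "The stratification used for randomization is the type of resection: left / right hepatectomy". The article does not say whether the list is blocked within strata, or why side was chosen.
- **Statistical methods.** The primary comparison is fixed: "The non-parametric Mann-Whitney u test will be used to compare the intraoperative BL values between both treatment groups". No stratum or covariate is mentioned here or for the secondary comparisons. The significance rule is two-sided at 0.05.
- **Sample size.** "53 patients have to be analyzed in each group to detect a 50% reduction of BL at a standard deviation of 94.1" per cent, with "an alpha of 5% and an 80% power level". The strata play no part in this calculation. The institution's retrospective blood loss figures are split by use of the Pringle manoeuvre, not by side.

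**The concern.** A stratification factor is normally chosen because it is thought to affect the outcome. If right and left hepatectomies bleed differently, part of the spread in blood loss is explained by side. A test that pools the two sides treats that explained spread as noise. When the arms are balanced within each side, the between-side difference cannot in fact contribute to a chance difference between arms. The plain test then uses too large a reference variance and rejects less often than it should. What is at stake is some power in the single confirmatory comparison, given up although the design already contains the information needed to keep it.

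This is not a gap that an unseen analysis plan would be expected to fill: the article names the primary test, and the test it names does not use the strata.

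**Working it through.** **1. The plan's own figure.** Inputs: reduction 50%, SD 94.1%, two-sided alpha 5%, power 80%.

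n per arm = 2 × (1.960 + 0.842)² × (94.1/50)² = 2 × 7.849 × 3.542 = 55.6, so 56 (57 with the t-test).

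With 450 ml and SD = 0.941 × 891 = 838.4 ml: 2 × 7.849 × (838.4/450)² = 54.5, so 55.

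The stated 53 is thus only approximately reproduced; power at 53 is 78.1% or 78.9%. With the Mann-Whitney efficiency under normality (0.955) it is about 75%. That shortfall is a separate matter. It is shown here only to fix the baseline.

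**2. What ignoring the strata does: closed form for normal data.** Assumptions not in the article: share of right resections π, right/left ratio of mean blood loss r, overall control mean 891 ml, SD 838.4 ml within each side (variance 702,967), exact 1:1 balance within sides.

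- Left mean = 891 / (πr + 1 − π); difference between sides Δ = left mean × (r − 1).
- λ = π(1 − π)Δ² / 702,967.
- The plain test behaves as if its critical value were 1.96 × √(1 + λ) instead of 1.96.
- Standardised effect at 53 per arm: (50/94.1) × √(53/2) × √0.955 = 0.5314 × 5.148 × 0.977 = 2.673.
- Power with strata: Φ(2.673 − 1.96) = Φ(0.713) = 76.2%.

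Example, r = 2 and π = 0.5: left mean = 891/1.5 = 594, Δ = 594, λ = 0.25 × 594² / 702,967 = 0.1255, critical value 1.96 × 1.061 = 2.079. Type I error = 2Φ(−2.079) = 3.8%. Power = Φ(2.673 − 2.079) = Φ(0.594) = 72.4%, a loss of 3.8 points.

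| r | π | λ | critical value | type I error | plain power | loss (points) |
|---|---|---|---|---|---|---|
| 1.25 | 50% | 0.014 | 1.974 | 4.8% | 75.8% | 0.4 |
| 1.5 | 50% | 0.045 | 2.004 | 4.5% | 74.8% | 1.4 |
| 1.5 | 65% | 0.037 | 1.996 | 4.6% | 75.1% | 1.1 |
| 2.0 | 50% | 0.125 | 2.079 | 3.8% | 72.4% | 3.8 |
| 2.0 | 65% | 0.094 | 2.050 | 4.0% | 73.3% | 2.9 |
| 2.5 | 50% | 0.207 | 2.154 | 3.1% | 69.8% | 6.4 |
| 2.5 | 65% | 0.148 | 2.100 | 3.6% | 71.7% | 4.6 |

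**3. Simulation with the actual rank tests** (106 patients, exact balance within sides, normal data, 50% reduction, plain versus van Elteren, 50% and 70% right resections):

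- r = 1: 75.3–75.7% versus 74.9–75.1%. Stratifying costs under 1 point when side does not matter.
- r = 1.5: 73.8–74.3% versus 74.8–75.0%.
- r = 2: 70.9–72.2% versus 74.4–74.5%.
- r = 3: 66.0–70.0% versus 75.0–75.1%.

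The closed form slightly overstates the loss at small r because it leaves out the small price of ranking within strata. At 70% right resections and r = 2 the simulated loss is 74.4 − 72.2 = 2.2 points.

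**4. Skewed data at the planned 50% reduction.** Log-normal with CV 0.8: both tests exceed 99% power. Log-normal with CV 94.1%: 98.5–98.6% versus 99.0–99.1% at r = 2, and 97.0–97.6% versus 99.0% at r = 3.

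**5. A smaller effect.** Log-normal, CV 0.8, about a 32% reduction, 50–65% right resections: 70–72% versus 78% at r = 2.0, and 64–65% versus 77–78% at r = 2.5. These are losses of about 6 to 13 points, but not at the planned effect.

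**6. Type I error.** With balance within strata, the plain test is at 3.4–4.2% for r = 2 and 1.6–3.4% for r = 3, across normal and log-normal data; the stratified test stays at 4.7–5.1%. Without that balance the plain test is at 5.0–5.2% for r = 1.5 to 2.5 in 6,000 trials per scenario. The simulation standard error is √(0.05 × 0.95/6,000) = 0.3 points, so this is the nominal level.

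**The case against.** The strongest reply is that nothing in the article shows side to be prognostic. There is no blood loss by side, no expected left/right mix and no stated reason for stratifying. At a ratio of 1.25 there is no material loss, and ratios of 2.0 or 2.5 have no source in the document. This stands, and it makes the consequence conditional.

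A reader might infer that the true type I error is below 5% as a matter of fact. The article does not support that. It requires side to be prognostic and also allocation balanced within strata, for instance by blocks, which the article does not describe. Without such balance only the power loss remains.

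A reader might also infer a loss of 6 to 13 points. Those figures need a reduction of about 32%, which is neither the planned 50% nor the 27.4% seen retrospectively. At the retrospective 27.4% the loss at ratio 2.0 is also appreciable (53% versus 61%), but power is then well below target with either test.

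Finally, one may say that the stratified analysis belongs in the analysis plan. That would be fair for a supportive analysis. It does not remove the mismatch, because the article itself fixes the primary test.

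**Conclusion.** The mismatch between the stratified design and the unstratified primary test is certain from the text. Its consequence is conditional and modest. If side is prognostic, the plain test gives up some power; if allocation is also balanced within strata, it is conservative as well. It does not inflate the type I error, so a positive result would not be misleading on this account.

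Under the normal model with the planned inputs, the loss is about 0 to 1 point for right/left ratios up to 1.5, 3 to 4 points at 2.0 and 5 to 6 points at 2.5, for 50–65% right resections and slightly less at 70%. Under a log-normal model at the planned effect it is negligible. The ratios, the left/right mix, the distribution and the exact balance are all assumptions. Whether to act depends less on the size of the loss than on the asymmetry: the stratified test costs almost nothing if side is irrelevant and recovers the loss if it is not.

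**What to change.** Before the data are analysed, replace the primary-test sentence under Statistical methods with one stating that intraoperative blood loss will be compared by a two-sided rank-sum test stratified by resection type (left/right hepatectomy). The van Elteren test is the natural choice; another rank analysis adjusted for the stratum would serve equally. Keep the unstratified Mann-Whitney test as a named sensitivity analysis.

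The cost is one sentence. No new data are needed, because type of resection is already recorded in the CRF, and the sample size need not change for this reason. In the simulations the price is under 1 point of power if side turns out not to matter. The date of the change should be recorded, since a switch made after seeing results by arm would look data-driven.

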**Methods:**

In a single center prospective, randomized, controlled, parallel, confirmatory trial the combination of PM and stapler resection technique in patients undergoing right and left hepatectomies will be tested against the control group that applies stapler resection without the use of PM. The primary endpoint of the study is the total intraoperative blood loss. The measurement of the intraoperative blood loss is conducted with respect to all handled rinse fluids during surgery and by weighing used swabs to generate accurate and comparable data. Secondary endpoints include intra- and postoperative blood transfusion requirements, liver function parameters and the 90-day mortality rate. A sample size of fifty-three patients in either group was calculated to detect a clinically significant difference in blood loss of at least 450 ml with an α of 5% at 80% power. The individual follow-up will be 90 days.

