### Trial duration

Based on the sample size calculation (2.4.1), the evaluation of the last patient will be completed (last patient out) 31 months after the start of screening for eligible patients (first patient in). Another three months later the results of the data analysis will be available. The individual duration of the trial for each patient is 91 days (randomization on the day of surgery, follow up 90 days postoperatively). Table 2 gives an overview of the trial schedule according to the SPIRIT statement [25].

**Table 2 Tab2:** Trial visits schedule

Trial visits					
Trial activity/examination	Preoperatively	Day of surgery	POD 1 and 3	POD 30	POD 90
Screening, informed consent, preoperative baseline data (Table 1)	X				
Type of resection (left/right hepatectomy)/BL/resection plane surface in cm^2^/number of transfused PRBC/duration of parenchymal resection/duration of PM/central venous pressure during resection/time from skin incision to completion of skin closure/protocol violations		X			
ALT/AST/total bilirubin/GGT/AP/INR/total albumin/numbers of transfused PRBCs/incidence of wound healing disorders/incidence and type of biliary leakage			X		
Incidence and type of wound healing disorders/incidence and type of biliary leakage/duration of hospital stay/mortality				X	
AE/SAE		X	X	X	
Mortality					X

*POD* Postoperative day, *BL* blood loss, *PRBC* packed red blood cells, *PM* Pringle Maneuver, *ALT* alanine aminotransferase, *INR* international normalized ratio, *AE* adverse event, *SAE* serious adverse event

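### Mortality is declared as a 90-day secondary endpoint, but the only mortality test the protocol article states is on 30-day mortality

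*Protocol article*

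**What the plan says.** Wherever the article defines mortality as an endpoint, the window is 90 days. The Abstract (Methods) lists "liver function parameters and the 90-day mortality rate" among the secondary endpoints. The Secondary endpoints section gives the same 90-day window, and Data collection has mortality recorded through day 90. The Trial duration section sets each patient's course as "randomization on the day of surgery, follow up 90 days postoperatively", and Table 2 there has a row for mortality alone, marked at POD 90.

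Table 2 also records mortality at POD 30, as the last item of the row "Incidence and type of wound healing disorders/incidence and type of biliary leakage/duration of hospital stay/mortality".

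Statistical methods contains one mortality comparison. Fisher's exact test is to "compare the rates of 30-day mortality, bile leakage, intraoperative transfusion requirements" and early postoperative transfusion requirements between the two groups. The threshold is the general one for the section: "Two-sided p-values < 0.05 will be considered as statistically significant".

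**The concern.** The article does not leave the mortality analysis open. It names a test and attaches a time point that differs from the declared endpoint. A statistician following the text would test a variable that is not a listed endpoint and would have no stated test for the one that is.

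What is at stake is the match between the endpoint and its analysis. The Objective section makes the safety of combining the Pringle manoeuvre with stapler resection a stated aim. In Table 2 the adverse-event row ends at POD 30, and mortality is the only item marked at POD 90. A mortality test that stops at day 30 therefore leaves the last scheduled safety assessment without a stated between-group comparison. The mismatch also means that either the 30-day or the 90-day figure could later be presented as the planned one.

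**Working it through.** The document gives no rate, power or sample size for mortality, so there is no figure of the plan's own to reproduce. The check is a comparison of the places that fix the time point.

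| Place in the protocol article | Role | Mortality window |
|---|---|---|
| Abstract, Methods | endpoint | 90 days |
| Secondary endpoints | endpoint | 90 days |
| Data collection | data recorded | to day 90 |
| Trial duration, Table 2, POD 90 column | visit | day 90 |
| Trial duration, Table 2, POD 30 column | visit | day 30 |
| Statistical methods | test | 30 days |

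**Step 1.** Both places that define the endpoint say 90 days. Thirty-day mortality can be computed from the POD 30 visit, but no section lists it as an endpoint.

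**Step 2.** The stated test covers days 0 to 30. The part of the endpoint window outside it is 90 − 30 = 60 days, or 60/90 = two thirds of follow-up. This is a share of time, not of deaths. The documents do not say how deaths are spread over the window.

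**Step 3 (illustration only).** To see how much a few deaths could move the test, take 53 patients per group from the Sample size section, assume all are evaluable, and put every death in one arm, which is the most extreme split. For k deaths against 0, the two-sided Fisher p-value is 2 × C(53,k) / C(106,k):

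| Deaths (0 v k) | Two-sided p |
|---|---|
| 0 v 3 | 0.243 |
| 0 v 4 | 0.118 |
| 0 v 5 | 0.057 |
| 0 v 6 | 0.027 |

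For k = 5: 2 × (53 × 52 × 51 × 50 × 49) / (106 × 105 × 104 × 103 × 102) = 2 × 0.0283 = 0.057.

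With five or fewer deaths by day 90, no split reaches p < 0.05 at either time point, so the choice of window cannot change the test result. With six or more it could. For example, 0 v 5 by day 30 and 0 v 6 by day 90 would cross the threshold. That needs an extreme imbalance and is not a prediction.

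**The case against.** The strongest case on the other side has four parts.

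- **The 30-day test may be an addition and not a replacement.** Table 2 collects mortality at POD 30. Statistical methods is not a one-to-one map of the endpoint list: it tests bile leakage, duration of surgery and hospital stay, which are not listed secondary endpoints, and names no test for the Clavien-Dindo complications, which are. This is a fair reading of how the section was written, but the article does not say that the 30-day comparison is extra. If it is, the declared endpoint still has no stated test.
- **A fuller plan may exist.** An unseen analysis plan may well test 90-day mortality. It would then disagree with this article's text, so the sentence would still need correcting.
- **Late deaths are not lost.** A reader might infer that deaths after day 30 disappear from the trial. The documents do not support that. They are recorded to day 90, belong to a declared endpoint, and meet the definition of a serious adverse event, which covers the whole follow-up period. They leave only the stated test.
- **Safety does not rest on this test alone.** A reader might also infer that the whole safety conclusion would be drawn from the wrong endpoint. The Objective section refers to perioperative outcome generally, and the listed endpoints include liver function, transfusion and complications as well as mortality.

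The last two points stand and limit the consequence. The first two explain how the mismatch could have arisen but do not remove it.

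**Conclusion.** The inconsistency is real and is wrong as written: a 90-day endpoint is paired with a 30-day test. It rests on the text alone and needs no outside figure.

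Its size is moderate. Mortality is one of eight listed secondary endpoints. The sample size is set on blood loss only ("53 patients have to be analyzed in each group to detect a 50% reduction of BL at a standard deviation of 94.1" percent), so the trial is not powered for mortality at either time point, and the primary analysis does not depend on it.

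It would go too far to say that the mismatch is likely to change the trial's conclusion on mortality. The documents give neither a mortality rate nor a share of deaths after day 30, and with a total of five deaths or fewer the test cannot be significant at either time point. The Fisher figures show scale only, on the assumption of 53 evaluable patients per group.

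**What to change.** In Statistical methods, change the mortality time point in the Fisher's exact test sentence from 30 to 90 days, so that it agrees with the Abstract, Secondary endpoints, Data collection and the POD 90 row of Table 2. If 30-day mortality is kept, say that it is additional to the declared endpoint. Date the change and make it before mortality is compared between the groups. If that comparison has already been made, report both time points and state which one was the declared endpoint.

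The cost is a one-line correction. The day-90 data are already collected, and neither the sample size nor the visit schedule changes. Reporting a risk difference with a confidence interval beside the test would be informative with so few expected events, but it is optional and not needed to resolve the inconsistency.

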### Safety/adverse events

#### Specification of adverse−/serious adverse events

“Adverse event” (AE) covers any sign, symptom, and syndrome, that appears in a subject during the follow up of the clinical trial and that may impair the well-being of the subject.

AEs will be recorded on a special AE form in the CRF. The following information will be recorded:Date of appearanceDescription of symptomDuration of AETreatmentSeverity code: mild, moderate or severePossible Relationship to trial treatmentOutcome

Symptoms that are commonly seen after major liver resections including postoperative pain, nausea and vomiting, delay of bowel movement, fatigue and lack of appetite will not be recorded as AE. AEs will be reported to the principle investigator in regular intervals throughout the study.

“Serious Adverse Event” (SAE) is **any** adverse event that occurs at any time during the follow up period, that results in death, is immediately life threatening, requires hospital admission, results in persistent or significant disability or incapacity or results in reoperation due to any reason. SAEs will be documented on a special SAE formula in the CRF and will be reported to the principle investigator within 24 h. The following information will be recorded:Date of appearanceDescription of symptomDuration of SAETreatmentSeverity code: mild, moderate or severePossible relationship to trial treatmentOutcome

SAEs which meet one of definitions of the secondary endpoints are treated as SAEs regarding to documentation but have not to be reported to the sponsor/principle investigator within 24 h. They will be reported to the principle investigator in regular intervals throughout the study.

## Discussion

PriMal StHep is the first randomized clinical trial to test the combination of PM and stapler resection technique as a means to reduce intraoperative blood loss in hemi-hepatectomies. The ongoing debate about potential adverse effects of PM in major liver resection is mainly attributed to extended durations of parenchymal dissection. As stapler hepatectomy has been proven to offer safe time- and cost-effective parenchymal dissection, the addition of PM to further reduce the intraoperative blood loss appears promising.

